## Intervention group

Participants in the intervention group will receive a structured Community-Based Intervention (CBI) in addition to standard medical care. The CBI is designed to provide holistic care by integrating education, yoga-based lifestyle modification, and home-based monitoring. The intervention will be delivered in groups of 8–10 participants, led by the same trained nurse facilitator throughout the study, with support from a certified yoga instructor for yoga sessions. The complete intervention will span 6 weeks, with sessions conducted six days per week.

### Pre-Intervention orientation and baseline assessment

The program will begin with a pre-intervention orientation and baseline assessment conducted by the nurse facilitator in a community hall within the selected slum, chosen for its accessibility of participants’ homes. Family participation will be encouraged but is not mandatory. During orientation, participants will receive education on essential self-care strategies for managing diabetes and hypertension, including maintaining physical activity, adequate rest and sleep, fluid balance, dietary modifications, adherence to prescribed medications, stress reduction, and avoidance of lifestyle risk factors such as tobacco use and excess sodium intake. To individualize the intervention, the nurse will apply the Transtheoretical Model of Behaviour Change, which includes the five stages of pre-contemplation, contemplation, determination, action, and maintenance. This approach will guide tailored goal setting and help match the intervention to each participant’s motivational readiness for adopting healthier behaviors.

### Yoga-Based lifestyle modification and nurse-led coaching

Following orientation, participants will engage in daily yoga sessions of a minimum of 30–45 min, six days per week, conducted in a local community hall by a certified yoga instructor. The yoga program includes warm-up exercises, selected postures such as Sukhasana, Vajrasana, Trikonasana, Paschimottanasana, Pavanamuktasana, Bhujangasana, and Shavasana, as well as breathing practices like Kapalabhati and guided relaxation or meditation. These practices are intended to reduce stress, improve flexibility, and enhance cardiometabolic health. Complementing yoga practice, weekly nurse-led group coaching sessions will be organized to reinforce educational messages, address adherence challenges, clarify misconceptions, and foster peer support. Coaching will be adapted to the participant’s stage of behavior change, providing informational support in early stages and motivational reinforcement during the action and maintenance stages. To enhance sustainability, ASHAs will assist in motivating participants to continue the practice throughout the intervention and beyond. Sessions will be scheduled at convenient times for participants and held in community halls close to their residences to ensure accessibility.

### Home-Based monitoring and follow-up reinforcement

To strengthen continuity of care, participants will be trained in home-based monitoring of blood pressure and blood glucose and will maintain a lifestyle diary documenting daily yoga practice, diet, and medication adherence. The nurse will provide follow-up reinforcement through weekly contacts in the first month and biweekly thereafter, conducted via home visits or telephone calls. During these interactions, the nurse will review self-monitoring records, reinforce educational content, troubleshoot difficulties, and provide motivational support. Participants who show poor adherence or worsening clinical indicators will receive additional counseling and relate to peer support strategies to encourage engagement and compliance.

## Control arm

Participants randomized to the control group will continue to receive routine medical care as prescribed by their physician. This care will include regular consultations with a physician, prescribed medications, routine monitoring of blood pressure and blood glucose, and general guidance on diet, physical activity, and lifestyle management. The control group will not receive any additional interventions, such as educational sessions, yoga-based activities, or nurse-led counseling. This design provides a clear comparator for assessing the effectiveness of the structured community-based intervention delivered to the experimental group.

## Randomization process

A total of 120 participants will be randomly assigned to either the intervention or control groups. To ensure balance in group sizes throughout the trial, block randomization will be employed using 12 blocks, each containing 5 participants allocated to the intervention group and 5 to the control group. The randomization sequences for each block will be generated using a computer-based random number list. An independent researcher, who is not involved in the intervention delivery or data collection, will oversee the randomization process. This researcher will be responsible for generating the allocation sequence and preparing the allocation concealment materials but will not directly assign participants to groups. Allocation concealment will be maintained by placing each assignment in opaque, sequentially numbered, sealed envelopes. These envelopes will only be opened after a participant has been formally enrolled in the study, ensuring that group allocation remains unpredictable and free from selection bias.

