**[name]:**

**[name] [name]:**

**[name] and [name] [name]:**

**[name]:**

## Specifications table

**Table utbl0001:** 

**Subject area**	Nursing and Medicine
**More specific subject area**	Community-based care for chronic diseases (Diabetes and Hypertension)
Name of protocol	Community-Based intervention (CBI) for Individuals with Coexisting Diabetes and Hypertension
**Reagents/tools / Instruments**	- Sociodemographic proforma and Clinical Profile Form - Digital Sphygmomanometer (BP measurement) - Standardized Glucometer (Random Blood Sugar Test) - Modified Diabetes and Hypertension Health Literacy Scale - 8-item Morisky Medication Adherence Scale (MMAS-8) - Modified Quality of Life Questionnaire
**Experimental design**	Randomized controlled trials (block randomization) with 1:1 allocation between intervention and control groups. **Intervention group:** Participants will receive the CBI, including: [1] pre-intervention orientation and baseline assessment, [2] yoga-based lifestyle modification and nurse-led counseling (6 days/week for 6 weeks), and [3] home-based monitoring and follow-up reinforcement. **Control group:** Participants will continue standard care and receive informational booklets on yoga and dietary management after intervention completion. Follow-up assessments will be conducted at 2 months, 3 months, and 6 months.
Trail registration	Registered in Clinical Trial Registry of India (CTRI/2024/08/071,775)
Ethics	Approved by Institutional Ethics Committee (IEC) of Institute of Medical Sciences and SUM Hospital, Siksha ‘O’ Anusandhan, Bhubaneswar, Odisha, India (Reference no: IEC/IMS.SH/SOA/2022/433). The study will adhere to the Declaration of Helsinki, ensuring voluntary participation, confidentiality, and participant safety.
Value of the protocol	1) Provides evidence on the effectiveness of a structured community-based intervention for patients with coexisting diabetes and hypertension. 2) Facilitates patient-centered care by integrating yoga, education, and home monitoring into routine treatment. 3) Offers insights for developing scalable interventions in urban slum populations to improve medication adherence, clinical outcomes, and quality of life.

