## Participants and enrolment

The study will be conducted in selected urban slum communities under the Bhubaneswar Municipal Corporation (BMC), Odisha. The selection of participants will be based on population density and the presence of active Non-Communicable Disease (NCD). In collaboration with local health authorities, the slums will be chosen to ensure adequate representation and logistical feasibility for data collection and intervention delivery. A community health survey will be conducted by a trained researcher in coordination with Accredited Social Health Activists (ASHAs) and Auxiliary Nurse Midwives (ANMs). All data collectors will undergo a structured two-day training program focused on participant screening, ethical considerations, informed consent procedures, and standardized data collection protocols.

The training will be supervised by senior investigators to ensure uniformity and quality assurance. Periodic field monitoring and random checks will be conducted throughout the study to maintain data reliability and adherence to protocol. Eligible participants will include individuals aged between 30 and 60 years who have been previously diagnosed with both diabetes mellitus and hyrtension. Verification of the diagnosis will be carried out through multiple sources, including review of patients’ medical records, confirmation in the NCD registers and the Health Management Information System (HMIS), and validation by the CHOs or healthcare workers based on available clinical documentation. Self-reported cases without medical record confirmation will not be included. All eligible participants will receive a detailed explanation of the study’s purpose, procedures, and potential benefits and risks. Written informed consent will be obtained before enrolment. Following enrolment, participants will be followed up within their community settings throughout the intervention and data collection phases to ensure consistent participation and outcome monitoring.

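### The blocks protect overall arm sizes but not balance within slums; envelopes stratified by slum would be a cheap improvement

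*Protocol article*

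**What the plan says.** The section on the randomization process states "A total of 120 participants will be randomly assigned to either the intervention or control groups". The method is given in the same section: "block randomization will be employed using 12 blocks, each containing 5 participants allocated to the intervention group and 5 to the control group". The purpose given is "To ensure balance in group sizes throughout the trial", and the specifications table confirms a design "with 1:1 allocation between intervention and control groups". No stratification factor is named.

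The section on participants and enrolment places the trial in more than one community: "The study will be conducted in selected urban slum communities". The data collection section and the limitations also speak of slums in the plural. Their number and the order in which they enrol are not stated.

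Delivery is local and in groups. The intervention section says "The intervention will be delivered in groups of 8–10 participants". Orientation and baseline assessment take place "in a community hall within the selected slum", and the yoga section puts the later sessions in halls near participants' homes.

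**The concern.** Slums can differ in access to care, in the local health workers who support the programme, and in living conditions. The control arm receives routine local care, so slum may well be related to outcome. Blocks taken from one list hold the arms level over successive enrolments. If several slums draw from that list at once, a block of ten is spread over them, and nothing keeps the split even within any one slum.

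At stake are some precision in the between-arm estimate, if slum matters and is not adjusted for, and the comparability of the arms within slums in the sample actually drawn. Once the envelopes are in use, the allocation can no longer be changed and only the adjustment in the analysis remains.

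**Working it through.** **Inputs from the article.** 120 randomised, 60 per arm; 12 blocks of 10, each 5:5; several slums.

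**Inputs assumed.** K equal slums of m = 120/K people, for K = 2 to 6. Enrolment is either concurrent (slums in random mixed order) or strictly slum by slum.

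**1. The stated scheme adds up.** 12 × 10 = 120 and 12 × 5 = 60 per arm. A scheme already stratified by slum and made of 12 complete blocks would need every slum to enrol a multiple of 10. One unstratified list is therefore the natural reading, though it is an inference.

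**2. Concurrent enrolment, one slum.** When slums arrive in random order, the number c of intervention participants in a slum of size m is hypergeometric: m drawn from 120, of whom 60 are intervention. Its variance is m × ½ × ½ × (120 − m)/119.
- K = 2, m = 60: 60 × 0.25 × 60/119 = 7.56, SD 2.75.
- K = 4, m = 30: 30 × 0.25 × 90/119 = 5.67, SD 2.38.

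The arms differ by |2c − m|. A difference of 6 or more means that c is at least 3 away from m/2. The exact probability is 36% for a slum of 60 and 29% for a slum of 30. With two slums both show the same difference, so 36% is also the chance that at least one does.

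**3. Concurrent enrolment, all slums.** Simulation of one list of 12 permuted blocks, 4,000 runs per setting:

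| Equal slums | Size | Mean of largest arm difference in a slum | Chance that some slum differs by ≥6 |
|---|---|---|---|
| 2 | 60 | 4.4 | 37% |
| 3 | 40 | 6.1 | 59% |
| 4 | 30 | 6.5 | 67% |
| 5 | 24 | 6.7 | 73% |
| 6 | 20 | 6.5 | 73% |

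A second run of 40,000 sequences gave 36%, 60%, 67%, 72% and 73%.

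**4. Slum-by-slum enrolment.** A difference arises only where the boundary between slums cuts a block. With 2, 3, 4 or 6 equal slums each size is a multiple of 10 and the difference is zero. With 5 slums of 24, the largest difference averages 2.6 and reaches 6 in about 2% of sequences.

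**5. What a difference of 6 means.** With two slums it is 33 against 27. Slum A then supplies 33/60 = 55% of one arm and 27/60 = 45% of the other. If mean outcomes in the two slums differ by D, the unadjusted estimate in that sample moves by 0.10 × D. D is not given, so the loss cannot be stated in outcome units.

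**6. Group size.** Exact balance gives 30/2 = 15 intervention participants per slum with 4 slums, and 24/2 = 12 with 5. One group holds at most 10 and two groups need at least 16, so neither 15 nor 12 divides into groups of 8–10. With 1:1 allocation in a slum, one group needs 16–20 enrolled there and two groups need 32–40. Group size therefore depends on enrolment per slum, and stratification alone does not settle it.

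**The case against.** The scheme contains no error. Its stated aim is balance in overall group sizes, which the blocks achieve. Unstratified randomisation is legitimate, and a condensed article may leave the number of slums, their order and any stratum to the full protocol. The figures also rest on assumptions about the number, size and mixing of slums. All of this stands, and it limits the point to an improvement on the scheme as described.

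Two stronger readings are tempting.

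- *The result would be biased.* A reader might infer confounding by slum. With individual randomisation, chance imbalance does not bias the estimate, and the error rate of the test already allows for it.
- *Some slums could not form a group of 8–10.* With concurrent enrolment, the chance that some slum has fewer than 8 intervention participants is 0% with 2 or 3 equal slums, 0.3% with 4, 10% with 5, 57% with 6 and 100% with 8 or more. With slum-by-slum enrolment, shortfalls appeared in the tested settings only from 8 slums upward. A range of 0 to 100%, set by an unstated number, shows no defect. The enrolment section also makes the feasibility of delivery a criterion for choosing slums. The hall within the slum is mentioned for orientation and baseline assessment, and no section confines a group to one slum.

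What the objection does not remove is that the randomization section describes its scheme in detail and ties it neither to slum nor to the forming of groups.

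**Conclusion.** The point holds as a modest design improvement. As described, the allocation does not protect balance within slums if they enrol concurrently, and differences of 6 or more in at least one slum would then be common: about 37% with 2 equal slums and 67% with 4. With strictly sequential recruitment the imbalance is small or nil. The consequence is some possible loss of precision and comparability, of a size the document does not allow one to compute. The conclusion rests on reading the 12 blocks as one list, on equal slums, and on mixed enrolment order. The planned total of 120 is unaffected.

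**What to change.** - Prepare one envelope series per slum, using small permuted blocks of varying size. Blocks of 10 within slum would still allow a difference of up to 5 in an incomplete last block.
- Include slum as a factor in the between-arm models.
- Reconcile the randomization section with the sections on delivery: state the number of slums, whether they enrol together or in turn, and how groups of 8–10 are formed from each slum's intervention participants.

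The cost is relabelled envelopes, one model term using K − 1 degrees of freedom for K slums, and a total that may end slightly off 60:60 because of incomplete last blocks. The envelope change has to be made before allocation starts.

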## Sample size

The sample size was calculated using the formula:$$N=\frac{2\sigma^{2}{\left(Z_{1-\alpha /2}+Z_{1-\beta }\right)}^{2}}{\delta^{2}}$$

Where:*N* = required sample size per groupσ² = pooled standard deviation of the primary outcome measure (assumed as 0.74 from prior studies)δ² = Anticipated difference in mean outcomes between groups (0.40)Z_1−α/2_ = standard normal variate corresponding to a 95 % confidence level (1.96)Z_1−β_ = standard normal variate corresponding to 80 % power (0.84)

By applying these values, the estimated sample size is approximately 54 participants per group. Considering a 10 % attrition rate, the final sample size will be 120 participants (60 in the intervention group and 60 in the control group).

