## Data collection plan and management

The initial survey will be conducted within selected urban slum communities to identify individuals diagnosed with both diabetes mellitus and hypertension. Eligible participants will be approached at their households to ensure accessibility and convenience. Trained community health workers, under the supervision of the research team, will carry out the survey following standardized procedures to ensure consistency and accuracy. After screening for eligibility and obtaining written informed consent, baseline data will be collected using structured interviews. Once baseline assessments are completed, participants will be allocated to either the intervention or control group using a computer-generated block randomization procedure. Follow-up data will be collected at multiple time points: baseline, 2 months, 3 months, and 6 months to evaluate both short- and mid-term outcomes.

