## Limitations

This randomized controlled trial has several limitations. First, it is conducted in selected urban slums, which may limit generalizability to rural areas or populations with higher socioeconomic status. Participants’ sociodemographic profiles will be documented to provide contextual interpretation of the findings. Second, blinding is not employed, and participants are aware of their group allocation, which may introduce performance bias, particularly in self-reported outcomes. To mitigate this, validated assessment tools will be used, and data will be collected by trained personnel who are not involved in the intervention. Third, the intervention relies on participants’ attendance at yoga and counseling sessions, as well as adherence to home-based monitoring. Variations in participation may influence outcomes; therefore, reminder calls, motivational support, and flexible scheduling will be implemented to enhance adherence. Fourth, potential confounding factors such as concurrent treatments, dietary changes, or lifestyle modifications cannot be fully controlled. Baseline assessments and ongoing monitoring will help account for these factors during analysis.

Additionally, given the study’s focus on urban slum populations, access to regular healthcare and diagnostic services may be limited. This could lead to underdiagnosis or delayed identification of chronic conditions, affecting the representativeness of the recruited sample. Consequently, the findings are most generalizable to similar urban, resource-constrained communities rather than broader urban or rural populations. Nevertheless, by leveraging existing public health infrastructure, including urban primary health centers, NCD registers, and frontline health workers, the study reflects real-world conditions and aims to generate contextually relevant evidence that can inform scalable community-based interventions in comparable low-resource settings.

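### A single disclosed block size of 10 in an unblinded trial makes some allocations deducible if enrolment is sequential, so the claim of unpredictable allocation is too absolute

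*Protocol article*

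**What the plan says.** The Randomization process section of the protocol article sets the scheme: "A total of 120 participants will be randomly assigned to either the intervention or control groups", and "block randomization will be employed using 12 blocks, each containing 5 participants allocated to the intervention group and 5 to the control group". No second block size and no stratification is described, and nothing says that the block size is withheld from field staff.

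A researcher independent of intervention delivery and data collection generates the sequence and prepares the envelopes, but does not assign participants. Concealment consists of "placing each assignment in opaque, sequentially numbered, sealed envelopes", opened only after formal enrolment. The section describes the result as "ensuring that group allocation remains unpredictable and free from selection bias".

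Two other places bear on this. Data collection plan and management gives the order of steps: "Once baseline assessments are completed, participants will be allocated to either the intervention or control group". Limitations states that "blinding is not employed, and participants are aware of their group allocation".

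**The concern.** An opaque envelope hides the next assignment from sight but not from inference. Inference needs two facts: the block size and the allocations already made in the current block. The first is printed in the article. The second is not protected by blinding, and attendance at group yoga sessions six days a week in a community hall makes membership of the intervention arm visible locally. Accredited Social Health Activists (ASHAs) help with the survey that finds participants (Participants and enrolment) and also motivate intervention participants to keep practising (Yoga-based lifestyle modification and nurse-led coaching). Some people close to recruitment may therefore know past allocations.

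Eligible people are approached at their homes, so there can be discretion over whom to approach or enrol next. Limitations recognises that results depend on attendance and adherence. A person's likely willingness to attend is therefore a conceivable basis for such a choice, and it could be related to outcome. Intention-to-treat analysis does not correct selective enrolment. Limitations offers mitigation for performance bias but does not mention selection bias, which the Randomization process section treats as excluded.

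**Working it through.** **Inputs.** Block of 10, 5:5; 12 blocks; 120 participants (all from Randomization process). Unblinded (Limitations).

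**1. The plan's own figure.** 12 × (5 + 5) = 120, and 12 × 5 = 60 per arm. This matches the stated total and the 60 per group in Sample size. It also uses up all 120 places, so every block has the same size.

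**2. Allocations that are certain beforehand.** Assume that the observer knows the block size and all earlier allocations, and that participants enter one at a time from one sequence. An allocation is certain once the other arm's five places are used. The number of certain allocations then equals the length of the final run of one arm in the block. There are C(10,5) = 252 equally likely orders, and a final run of length r occurs in 2 × C(9 − r, 5 − r) of them:

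| Final run r | Orders | Share of blocks |
|---|---|---|
| 1 | 140 | 55.6% |
| 2 | 70 | 27.8% |
| 3 | 30 | 11.9% |
| 4 | 10 | 4.0% |
| 5 | 2 | 0.8% |

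- Mean: (140×1 + 70×2 + 30×3 + 10×4 + 2×5) / 252 = 420/252 = 1.67 per block. The general formula 2m/(m + 1) with m = 5 gives the same, 10/6.
- Over 12 blocks: 12 × 1.67 = 20 of 120, or 16.7%.
- Minimum: one per block, 12 of 120.
- At least the last two are certain in 112/252 = 44.4% of blocks.

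**3. Best guess.** Always guess the arm that is behind, and toss a coin at a tie. Expected correct guesses per block are 5 + (4^5/252 − 1)/2 = 5 + (4.063 − 1)/2 = 6.53 of 10, or 65.3%. An unpredictable sequence gives 50%.

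**4. Comparison with other fixed sizes.** The certain share is 1/(m + 1): 1 in 3 for blocks of 4, 1 in 4 for blocks of 6, 1 in 6 for blocks of 10.

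**5. What varying the size achieves.** The size sets here are assumptions for illustration. Sizes were drawn at random by simulation, with an observer who knows the set of sizes but not their order.

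| Sizes | Certain allocations of 120 | Share |
|---|---|---|
| 10 only (plan) | 20 | 16.7% |
| 4, 6 | 6.5 | 5.5% |
| 4, 6, 8 | 2.7 | 2.3% |
| 6, 8, 10 | 1.9 | 1.6% |

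If the set of sizes is also withheld, no allocation is certain to the recruiter.

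Varying the size does not remove the guessing advantage. Every block ends in balance, so the arm that is behind can be read from the running totals without knowing the size. Expected correct guesses are 4.10, 5.33 and 6.53 for blocks of 6, 8 and 10. An equal mix therefore gives about (4.10 + 5.33 + 6.53)/24 = 15.96/24 = 66.5%, close to the 65.3% above. Randomising a completed batch in one step removes both forms of foreknowledge, because nobody is left to select once the first allocation in the batch is known.

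**The case against.** The strongest reply is that the one-in-six figure describes a fully informed recruiter, and the article does not describe such a person. It does not say who opens the envelopes. That the independent researcher does not assign participants shows only that someone else does. It does not say that recruiters see the running sequence, and recruitment covers several slum communities, so one field worker need not see every allocation in order. The text also fits batch allocation: a survey, then consent and baseline, then allocation, with the intervention delivered to groups of 8–10. If whole blocks were consented and assessed before any envelope was opened, foreknowledge could be zero. All of this stands, and it makes the figures conditional.

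A second reply points to the safeguards: independent generation, opaque numbered envelopes, opening after enrolment, and baseline before allocation. They narrow the scope for manipulation but do not stop deduction towards the end of a block, because the choice at risk is whom to enrol next.

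A third reply is that outcome measures are recorded before allocation, so imbalance on them can be seen and adjusted for. That is true of measured variables. It does not reach unmeasured motivation.

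Finally, 10 is a fairly large fixed block and is less predictable than 4 or 6. That limits the seriousness but does not rescue an absolute statement.

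**Conclusion.** The point holds in conditional form. One fixed, published block size in an unblinded trial does not support the statement that allocation stays unpredictable and free from selection bias. If enrolment is one at a time from a single sequence and someone involved in recruitment knows the earlier allocations, at least 12 of 120 allocations are deducible, 20 of 120 (17%) on average, and the best guess is right about 65% of the time. If whole blocks are enrolled before any envelope is opened, the figure can fall to zero.

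A reader might infer that recruiters will know one allocation in six, that field staff open the envelopes, or that enrolment will be biased. The article supports none of these: it leaves the enrolment pattern, the opener of the envelopes and the recruiters' knowledge unstated. The weakness is moderate, avoidable and cheap to correct. It does not invalidate the design.

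**What to change.** Make one of two changes in the Randomization process section.

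- **Varying blocks.** Replace the 12 fixed blocks of 5+5 with computer-generated permuted blocks of randomly varying size. State that sizes and order are held only by the independent researcher, and do not print the sizes. This removes most or all certain allocations, though not the advantage of guessing.
- **Batches.** State that all members of a recruitment batch complete consent and baseline before any envelope in that batch is opened, and randomise each batch 1:1 in one step. If this is already the practice, saying so largely resolves the point.

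In either case, name by role who opens the envelopes, and soften the sentence that guarantees unpredictability. If recruitment has begun, apply the change to the remaining allocations.

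The cost is a new list and a new set of envelopes. With varying blocks the final arms may differ slightly from 60:60. With batches, early recruits wait until their batch is complete.
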